### 4.2 Anticipated adverse device effects

Adverse effects of digital support for behavior change are not obvious, and none have been reported in the scientific literature as far as we are aware. A systematic review including 113 RCTs investigating healthy diet and physical activity counselling reporting on adverse effects found no evidence for greater harm in the intervention versus the control group (33). Nevertheless, there are some identified concerns associated with the use of digital services for behavior change. The main risks that concern end-users are related to data security and confidentiality, reliability of the device,

and trustworthiness of the manufacturer (2, 23). Demotivation, self-confidence, self-consciousness, factors interrupting tracking, and data inaccuracy are common reasons for discontinued use (14).

Additional risks are increased screen time, perceived stress and excessive exercise and eating behaviors, potentially leading to orthorexia, and eating disorders. Filling out forms about mental health status and lifestyle behaviors may give rise to anxiety and low self-esteem. Not reaching self-identified goals and lack of expected results may cause a feeling of failure and hopelessness. Chat groups may be used to harass other subjects and encouragement and feedback can be misunderstood by subjective interpretation. Ultimately, behavior change will improve clinical values (e.g. blood lipids, metabolic control, blood pressure, pain, and sleep). Individuals on medication would conceivably need to adjust the dose of medication. There is a risk for relapse in behavior change and to re-adjust the medication.

#### 4.3 Risks associated with participation in the clinical investigation

Study subjects register for the digital service on the premises to use it as a consumer product, not to be involved in research. Upon registration a request to participate in the research study is shown in the app with information about the research study and obligations of participation (supplement 5a Forskningspersonsinformation). Study subjects consent to share their data for research purposes and will be asked to answer questions in the app that has been provided by researchers. This may cause stress and distraction to the user's intended use of the service for improved health and well-being, and increased concerns about private privacy as the data will be transferred to the researchers and used for research purposes.

Except for the before mentioned adverse device effect, no other risks have been identified for subjects in the clinical investigation.

#### 4.4 Possible interactions with concomitant medical treatments as considered under the risk analysis.

The risk of interactions with eventually concomitant medications is low. The subjects will be recommended to keep in contact with their responsible clinician to adjust medications if necessary.

#### 4.5 Steps that will be taken to control or mitigate the risks.

The risks of data insecurity will be handled cautiously, and the subjects will be informed about the measures taken to secure confidentiality and trustworthiness with an informed consent. The system is built to never share any personal data with any party, applying pseudonymization with anonymous ID numbers for all users. Personal data will be stored in a double-encrypted, three-level categorization system to ensure data security, and personal integrity by separating personally identifiable information from personally sensitive information. The system has strictly limited access to personal data with regulated, monitored, and logged functions that enable access to limited and anonymous data for authorized parties only. For example, authorized researchers and health coaches must identify themselves with electronic identification to access strictly limited and anonymous data, only relevant to research or health coaching purposes. Overall, the system complies with the current requirements for security and monitoring, which is ensured by regular security checks and penetration testing by an external independent party.

The risk of perceived stress, excessive behaviors, anxiety, a feeling of failure, hopelessness, and low self-esteem are mitigated through support by setting realistic and progressive goals, encouragement, information, and webinars about behavior change and healthy habits. Alerts and report functions are built into the system to alarm excessive habits and low well-being score. World Health Organization's well-being index (WHO-5) (34) will be sent out monthly to the user. When low well-being is reported (score 50 or below) recommendations to healthcare providers is presented to the user.

A requirement for working as a health coach is owning a higher-level education as a health professional including at least 7.5 ECTS in health counselling. A mandatory introduction course for all new health coaches is produced by the Head of health coaching and Quality manager and covers elements of mandatory security measures based on the risk assessment. Prior to the coach session, the coach gets data on the user's action plan covering well-being scores and details about the user's action plan. A protocol and a guide for how and where to refer individuals in need of health care have been produced by the quality manager.

To prevent bullying and harassment between users, LongLife Actives health coaches manage and monitor the community. Also, alert and report functions are built into the system for users and coaches to alarm discourage and inappropriate posts in the community.

Overall, risk management activities will systematically be performed following the ISO 14155 framework throughout the clinical investigation. The identified residual risks will regularly be monitored and analyzed to ensure sufficient security measures. A Monitoring plan has been developed which covers processes of all risk management activities and security measures based on the risk assessment including operative guidelines for LongLife Actives health coaches. The Quality manager is responsible for risk management and educates all stakeholders involved in risk management activities.

#### 4.6 Rationale for the benefit-risk ratio.

Expected benefits of the medical device outweighs the potential risks. On the first hand, there are anticipated benefits on well-being and behavioral outcomes. In addition to these anticipated benefits, previous studies have reported further empowerment and health literacy benefits of digital

interventions in relation to self-management. Examples of benefits are improved decisions making skills concerning the own health, perceived facilitation of self-management, an understanding of self-monitoring readings, increased awareness, a sense of control over a condition, and improved motivation to continue self-management activities (35). In this study the subjects will set self-identified goals and decide for themselves of a weekly plan for how to reach the goals in their own pace. Suggestions, encouragement, inspiration, and feedback will be tailored to preferences and identified needs of each individual. These are factors that potentially lead to improved empowerment and health literacy.

#### 4.7 Data monitoring committee

The Data monitoring committee consists of the sponsor ([name]) and investigators ([name], [name] and [name]). Monthly meetings are arranged unless more often is needed.

### 5. Objectives and hypothesis of the clinical investigation

#### 5.1 Main objective

I) The primary objective of this project is to evaluate the effectiveness of an individually tailored digital service aimed to support healthy habits among the adult population on well-being compared to a control sample of the general population.

#### 5.2 Secondary objectives

II) To study internalization and implementation factors such as reach and dose of the medical device across 6 months.

III) To explore the impact of three different levels of digital support for healthy habits on reaching self-identified goals, dietary and physical activity habits, and mental health after 6 months.

IV) To explore determining response of sociodemographic factors in meeting the self-identified goal, dietary and physical activity habits, mental health, and well-being.

V) To evaluate the intended mediators (engagement with the service, improved motivation, self-efficacy, and reduced perceived barriers) of the medical device on achieving the self-identified goal, improved dietary and physical activity habits, mental health, and well-being.

VI) To explore what app functions and features mediate improvements of the medical device on behavior change, mental health, and well-being.

VII) To explore the engagement of using the digital service and adherence to behavior change across 24 months.

VIII) To explore the patterns of achieving the self-identified goal, change in motivation, dietary and physical activity habits, mental health, and well-being across 24 months.

### 5.3 Hypotheses

1. The mean well-being score at 6 months of intervention is  $\geq 12$  score points higher in the intervention groups compared to the control group.
2. The impact on well-being is slightly stronger in the groups with higher level of support (Standard and Premium) compared to the group with lower level of support (Basic).
3. The medical device improves the individually targeted dietary habits, physical activity, and mental health among users at 6 months intervention compared to start of intervention.
4. Motivation, self-efficacy and achieving the self-identified goal mediate the effects of using the digital service on dietary and physical activity habits, mental health, and well-being.
5. The engagement with the service levels of across 24 months intervention for the group with less support (Basic) but maintains in the two groups with higher level of support (Standard and Premium).
6. The intervention effects on behavior change and well-being are maintained over 24 months in the two groups with higher levels of support (Standard and Premium) compared with the group with less support (Basic).

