This study is a real-world post-market observational clinical investigation with a control group aimed to evaluate the impact of a digital service in improving well-being by supporting healthy lifestyle habits. A four-armed control condition will allow comparison between a control group recruited among the general population, and three levels of intervention among subscribers. The levels of intervention are I) core functions include self-monitoring, goal setting, action planning, an AI chat and databases with recipes and exercises; II) the same core functions + social support; II) the core functions + social support + individual counselling by a professional health coach. Randomisation of subjects to the different allocation arms is not appropriate because the users or their employers will pay for the digital service and thus choose the level of support.

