### 7.3 Analytical procedures

Change in the endpoint well-being (as total score) and the intermediate outcomes dietary habits, physical activity, and mental health, will be analysed across time and between groups using mixed model for repeated measures, and reported as estimates with confidence intervals. The model will include intervention level and time (0, 6, 12, 18 and 24 months).

To investigate correlations and associations of demographic factors and user engagement with behavior change, mental balance, and well-being, structural equation modelling and mixed models will be applied.

Regression analysis and mixed models will be applied to evaluate mediating factors and responsiveness. These analyses will explore if high levels of motivation, self-efficacy and reduced perceived barriers mediates improvements in reaching the self-identified goal, behavior, mental health, and well-being and whether improvements in motivation, behavior, and mental health mediate well-being. Cut off values for the intermediate outcomes will be derived based on baseline values and findings from similar studies.

The threshold for statistical significance will be set at  $p < 0.05$ .

Qualitative data (chat groups and dialogues with included actors) will be analyzed by content analysis (46).

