### 7.4 Sample size calculation

The endpoint well-being will be assessed using the WHO-5 Well-being Index (34). In our pilot study the mean score at baseline was 55. The instrument has to our knowledge not been applied on a general Swedish population. In Danish general population surveys, the mean WHO-5 score was 60-70 ( $sd=19.0-19.9$ ) (36, 47, 48). A change of 10-20 points in WHO-5 has been proposed as a clinically relevant change (36, 49). In up-scaled interventions 60% lower effects are expected (50). We therefore aim at a difference of 12 points in the score between intervention groups and control group as well as between baseline and 6 months. A fluctuation in well-being is considered normal (36), subjects with well-being score  $>70$  are not expected to improve and will be excluded from the analysis. In the pilot study 21% of participants reached 70 points at baseline.

Desirable sample size was calculated to detect an effect of 12 points (36, 51) based on the assumption of two-tailed testing, an alpha error  $\alpha=0.05$  and power  $1-\beta=0.90$  and  $sd=19.9$  (48). To detect a medium standardised effect size of 0.5 (Cohen's d) for the primary outcome well-being at 6 months a sample size of at least 25 subjects per group is recommended. Expected drop-out rate due to withdrawal and lost to follow-up at six months is 75 %. Based on the expected drop-out rates and on excluding 20% from the analysis due to baseline score  $>70$ , we need to recruit at least 500 subjects to assure 25 subjects in each intervention arm. In the control group we assume subjects to be excluded based on using a digital product for behavior change and strive to include 200 subjects.

The secondary outcomes are exploratory due to the person-centred design of the service. The subjects will set individual goals and possibly change goals during the intervention. Likewise, habits and behavior change are largely changeable due to circumstances. The current research is not immense enough to guide a decision for minimal expected effects when individual goals are set (e.g., reducing weekly servings of red meat). A larger sample size than what is required for the primary

endpoint well-being is desired. Similarly, the secondary analyses of mediating factors and responsiveness require a large sample size. We therefore aim to include 5000 subjects.

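### The protocol conflicts on whether the primary comparison pools the three service levels or tests each against control, and section 7.4 adds an unranked 12-point target from baseline

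*Protocol*

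**What the plan says.** The synopsis (1.6) fixes well-being at 6 months as the primary endpoint, and 7.4 names the WHO-5 as its measure. The places that bear on the primary contrast are these.

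- **5.1 Main objective.** The aim is "to evaluate the effectiveness of an individually tailored digital service" and its effect "on well-being compared to a control sample of the general population". This is one service and one comparator.
- **3.1 Rationale.** "A four-armed control condition will allow comparison between a control group recruited among the general population, and three levels of intervention among subscribers".
- **5.3, Hypothesis 1.** The 6-month mean is at least 12 "score points higher in the intervention groups compared to the control group". The plural does not say whether the groups are pooled, taken one at a time, or all required to reach the margin.
- **7.3 Analytical procedures.** "The model will include intervention level and time (0, 6, 12, 18 and 24 months"; no pooled user-versus-control term is mentioned. "The threshold for statistical significance will be set at" p<0.05, with no distinction between tests.
- **7.4 Sample size.** The aim is a "difference of 12 points in the score between intervention groups and control group as well as between baseline and 6 months", and the recruitment figure is set "to assure 25 subjects in each intervention arm". The exploratory label in this section is attached to the secondary outcomes, not to further tests of well-being.

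**The concern.** Two separate matters are left open in the protocol's own text.

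The first is how the three levels form the primary comparison. The pooled, any-level and every-level readings are different tests with different error rates, and each finds support in the wording. Users choose their level, so the mix in a pooled estimate is not controlled. Hypothesis 2 expects some difference by level, so the readings need not agree.

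The second is the standing of the baseline comparison. Section 7.4 gives it the same 12-point margin as the comparison with control, in the same sentence. A change from baseline in users alone has no control for drift, and here drift is built in: the primary analysis drops everyone scoring above 70 at the start, so the remaining group's mean is expected to rise even if the app does nothing. If that change could be offered as support for the primary aim, the control group would lose its purpose.

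**Working it through.** **1. The plan's own figures.** The protocol states no family-wise error, so there is none to reproduce. The recruitment figure in 7.4 shows how the levels were treated. With 75% drop-out and 20% excluded, one group of 25 needs 25 / (0.25 × 0.80) = 125 recruits. Four groups need 4 × 125 = 500, the stated minimum; three would need 375. The sizing therefore treats each level as its own group. The figure of 25 is used here only for that structure. A two-sample calculation with 12 points, SD 19.9, two-sided 0.05 and 90% power gives 58 per group, which is a separate matter.

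**2. Family-wise error for three levels against one control.** Inputs: |z| > 1.96 for each test, no true effect in any level, equal variances, normal group means, 2 million simulated trials. Evaluable users: 5000 × 0.25 × 0.80 = 1000. Evaluable controls: 200 × 0.25 × 0.80 = 40, assuming that the same losses apply to controls. The split over levels is not given, so several are shown. Each contrast is z = (level mean − control mean) / (SD × √(1/n_level + 1/n_control)). The shared control makes the contrasts correlated, at 0.5 with equal groups and 0.89 with 333 per level and 40 controls.

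| Evaluable numbers (levels; control) | Any level significant, two-sided | Any level significant, in the device's favour |
|---|---|---|
| 25, 25, 25; 25 | 12.5% (12.6% in another run) | 6.3% |
| 333, 333, 333; 40 | 8.5% | 4.2% |
| 700, 200, 100; 40 | 9.4% | 4.7% |
| 800, 100, 100; 40 | 9.9% | 5.0% |

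The reference values for one test are 5% two-sided and 2.5% in the device's favour. A single pooled contrast gives 5%. Requiring every level to be significant gives at most 5%.

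**3. Change from baseline with no device effect.** Inputs: pilot baseline mean 55 and SD 19.9 (both in 7.4), cut-off 70, normal scores. The correlation r between baseline and 6 months is not in the document; 0.5 to 0.8 is assumed.

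- Standardised cut-off: a = (70 − 55) / 19.9 = 0.754. The share above it is 22.5%, close to the 20% to 21% in 7.4.
- Mean of those retained: 55 − 19.9 × φ(a)/Φ(a) = 55 − 19.9 × 0.3003/0.7745 = 55 − 7.72 = 47.28.
- Expected rise with no effect: (1 − r) × 7.72.
- Variance of change: (1 − r)² × 220.7 + (1 − r²) × 19.9², where 220.7 is the baseline variance after the cut.

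| r | Expected rise | SD of change | SE, n = 1000 | z | Chance of p<0.05 |
|---|---|---|---|---|---|
| 0.5 | 3.86 | 18.77 | 0.593 | 6.50 | >99.9% |
| 0.8 | 1.54 | 12.30 | 0.389 | 3.97 | 97.8% |

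With 333 users in one level, the chance is 96% at r = 0.5 and 63% at r = 0.8.

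**The case against.** The strongest reply is that the primary question is already settled. One endpoint, one time point and one comparator are stated, 5.1 speaks of a single service, and Hypothesis 1 is purely between-group. Order of testing and adjustment are commonly left to a statistical analysis plan, which is not shown. The study is non-randomised and post-market, and it reports estimates with confidence intervals.

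Much of this stands. A missing alpha hierarchy would not be a finding by itself. A reader might infer three stronger points, and the document supports none of them:

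- **That Hypothesis 1 itself contains the baseline target.** It does not. The target is in 7.4, worded as a planning aim.
- **That the study's error rate is 8% to 23%.** The upper end needs eight candidate successes (three levels and the pool, each against control and against baseline), which together give 22% to 23% under a global null. The protocol nowhere says that any one of them would suffice, and about half of those errors would go against the device.
- **That the pooled and level results are likely to contradict each other sharply.** Hypothesis 2 expects only a slight gradient with more support, and no level mix is given. An example with a large gradient and a lopsided mix would rest on invented inputs.

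It is also fair to say that a rise of 1.5 to 3.9 points is far short of 12, so a reader who applied the margin strictly would not be misled by it.

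The reply does not remove the conflict between 5.1 and the per-level text in 3.1, 7.3 and 7.4, or the two unranked 12-point aims. Both are in the protocol and should be settled there.

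**Conclusion.** The point holds as a conflict of wording with a conditional consequence, and it should be fixed. What is open is how the three levels enter the primary comparison and what role the baseline comparison has.

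The 8.5% to 12.6% (about 4% to 6% in the device's favour, against 2.5%) applies only if one significant level were accepted as success, with no true effect in any level and the assumed group sizes. It is not the study's error rate.

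The regression-to-the-mean result rests on approximate normality, the pilot mean, a population SD and an assumed correlation. Over the range shown, a test of change from baseline in about 1000 users is significant almost regardless of what the app does. The comparison with control is better protected because controls are cut at the same score, though the drift cancels only so far as the two baseline distributions are alike.

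**What to change.** - **5.3 and 7.3:** state that the primary contrast is all intervention users combined against control in WHO-5 at month 6, matching 5.1, at two-sided alpha 0.05, with users weighted as enrolled.
- **5.3 and 7.3:** report Basic, Standard and Premium each against control as secondary, with a Holm or Dunnett adjustment.
- **7.4:** remove the baseline-to-6-month difference as a target, and report change within users descriptively with a confidence interval.

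The cost is wording only, with no extra subjects or data. There are three downsides. A claim for a single level would need an adjusted p-value (under Holm, the smallest of three below 0.05/3 = 0.0167). A pooled contrast can dilute an effect confined to one level, more so if few users choose that level. Change from baseline alone could no longer be presented as success.

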## 6. Design of the clinical investigation

### 6.1 Investigational device/Description of exposure

The medical device to be investigated is the mobile phone application (app) LongLife Active®. The app includes three core topics: 1) Healthy diet, 2) Physical activity, and 3) Mental balance. Supplement 4 shows the included intervention components and behavior change techniques. The service includes functions such as tracking and self-monitoring behavior and health outcomes, goal setting, action planning, a database with food recipes, a database with exercises, a database with relaxation exercises, skills training articles and webinars, live events, adjustable push notifications and gamification (rewards). If the user prefers there are options to pay extra for further social support: a version including a community (chat groups and group coaching sessions, live events and physical meetup events), and a version including the community plus the possibility to have a private health coach. The app is assisted by artificial intelligence to direct the support to the individual timely and based on the needs, motivation, preferences, experiences, opportunities, and capabilities of each user. The user decides which functions to use.

The literature review undertaken during the formative phase showed participants wished for interface design and reminders to be customizable, and that the service should be integrated with other services (such as shopping lists). These are examples of aspects that have been regarded to keep engagement over time. With a straightforward design, illustrations, and short video instructions the service is customized for people with low skills in the Swedish language or with low digital and/or health literacy.

No other medical devices or medications are to be used.

